#### Qualitative Component

For the analysis of the qualitative component of the study, the audio-recorded FGDs and in-depth interviews will be transcribed by multiple investigators. The transcripts will be reviewed thoroughly and exported to NVivo software (QSR International). Reflective thematic analysis based on a framework or template approach will be used to analyze the transcripts. Inductive coding of the transcripts will be performed independently by 2 investigators trained in qualitative research, and they will engage in regular analytic discussions to surface assumptions and enhance reflexivity, while field notes will document decisions and researcher positionality. Member checking approach and audit trails will be used to establish credibility and confirmability. A third independent investigator may review the transcribed data to increase the study’s internal validity. Intercoder agreement will be performed to enhance the validity of the study. The codes obtained from the transcripts will be thoroughly reviewed, and the codebook will be generated. The codes will then be merged to form categories, subthemes, and themes and categorized as either facilitators or barriers. Dependability will be addressed through an explicit coding manual and transparent documentation of the analytic steps, while transferability will be supported by providing rich, contextualized descriptions of the participants and selection of study participants.

The statistical analysis to evaluate the costs incurred in implementing CMR in the Indian health care setting from a health system perspective includes direct, indirect, and opportunity costs. Data collected from various facilities will be cleaned and entered into a predesigned database. All costs will be standardized to 2025 prices by using the consumer price index for health care services. Descriptive statistics will summarize continuous variables such as salaries and utility costs by using the measures of central tendency (mean, median) and dispersion (SD, IQR), while categorical variables such as facility type will be reported as frequencies and percentages. Comparative analyses will assess cost differences between public and private sector facilities by using independent-sample 1-sided *t* tests for normally distributed data or Mann-Whitney *U* tests for nonnormally distributed data. To explore the predictors of the cost variations across facilities, we will conduct multivariable linear regression with total CMR costs as the dependent variable and facility characteristics, human resources, and infrastructure costs as the independent variables. Interaction terms such as facility type and operational hours will be included to investigate the moderating effects. All statistical analyses will be performed using STATA (version 18), and *P* values less than .05 will be considered as statistically significant.

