## Methods

### Study Settings

This study is planned to be conducted over a period of 2 years in 5 phases chronologically (Figure 1). The study will be conducted at the Pondicherry Institute of Medical Sciences and Jawaharlal Institute of Postgraduate Medical Education and Research, Puducherry, India, in collaboration with Indian Council of Medical Research (ICMR)-National Institute of Epidemiology, Chennai, India, and ICMR headquarters, New Delhi. The scoping review (phase 1) on CMR is completed.

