#### Study Participants

Health care providers at the 2 sites will be involved in the study to assess the facilitators and barriers in the implementation of interdepartmental CMR from their perspective. The prescriptions of both male and female older patients (aged 60 years and older) admitted to any medical or surgical ward at both study sites will be assessed to determine whether the participants meet the eligibility criteria after the medical records are reviewed.

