### Sample Size Estimation and Analysis

The sample size calculation for the assessment of CMR efficacy was based on a previous study [1], which showed that the prevalence of potentially inappropriate medications in the older adult population was 28% in India. We assume that the effect size of the interdepartmental CMR is 10%, power is 80%, and significance level is 5%. The sample size calculation was estimated to be 280 participants. Given that this study will be conducted at 2 different sites, Pondicherry Institute of Medical Sciences and Jawaharlal Institute of Postgraduate Medical Education and Research, 140 participants will be recruited from each site. Universal sampling techniques will be used to enroll participants in this phase of the study. For the qualitative component of the study to assess the implementation challenges of CMR, preferably 2 FGDs will be conducted among CMR team members at each study site. Approximately 10-16 in-depth interviews will be conducted per site until the data saturation point is reached.

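### The planned public-versus-private cost test and facility-level cost predictors have no replication in a two-hospital study: any such effect is aliased with site

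*Protocol article*

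**What the plan says.** Three sections of the protocol article fix the number of sites. Study Settings: "The study will be conducted at the Pondicherry Institute of Medical Sciences and Jawaharlal Institute of Postgraduate Medical Education and Research"; the other two bodies named there are collaborators. Study Participants: "Health care providers at the 2 sites will be involved in the study". Sample Size Estimation and Analysis: "Given that this study will be conducted at 2 different sites", followed by "140 participants will be recruited from each site".

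The cost paragraph, printed under Qualitative Component in Data Management and Statistical Analyses, reads as if there were a sample of facilities:

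- Sector test: "Comparative analyses will assess cost differences between public and private sector facilities", by "independent-sample 1-sided *t* tests for normally distributed data or Mann-Whitney *U* tests for nonnormally distributed data".
- Regression: "To explore the predictors of the cost variations across facilities, we will conduct multivariable linear regression with total CMR costs as the dependent variable", with facility characteristics, human resources and infrastructure costs as covariates.
- Moderation: "Interaction terms such as facility type and operational hours will be included to investigate the moderating effects".

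Significance is judged at P below .05. The paragraph speaks of data from several unspecified facilities, but no section names a third facility where CMR is delivered or costed. The article gives neither hospital's sector, nor the unit of analysis for cost.

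**The concern.** A sector effect, or a predictor of cost across facilities, is a statement about facilities, so its precision depends on how many facilities there are. With one hospital per sector, the sector difference and the ordinary difference between any two hospitals are the same number, and nothing in the data separates them. Choosing another test or another covariate set does not change that.

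Two outcomes are likely. The software may return undefined or dropped terms. Or the analyst may compare 140 with 140 patients and report the P value as a public/private difference. The second is the more harmful. Implementation cost is the first-listed secondary end point, and the Discussion presents the economic results as directly relevant to policy makers. The article does not tie that relevance to the sector contrast, but a printed sector P value invites the reading.

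**Working it through.** **Inputs.** Two hospitals, 140 participants each; 2 × 140 = 280, which matches the stated total. The article gives no sample size for the cost analysis. Test, regression terms and significance level are as in the cost paragraph. Assumption: one hospital is public and one private, the only split of two that allows a sector comparison. The interaction is read as the product of facility type and hours.

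**1. Facility as the unit, as the paragraph words it.**

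- t test: degrees of freedom = n1 + n2 − 2 = 1 + 1 − 2 = 0, so P is undefined.
- Mann-Whitney: smallest one-sided exact P = 1/C(n1+n2, n1). The article does not state sidedness for this test; one-sided is the favourable case.

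| Facilities per sector | Smallest one-sided P |
|---|---|
| 1 v 1 | 1/2 = 0.50 |
| 2 v 2 | 1/6 = 0.167 |
| 3 v 3 | 1/20 = 0.05, not below .05 |
| 4 v 4 | 1/70 = 0.014 |

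With equal numbers, P below .05 is out of reach with fewer than four facilities per sector.

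- Regression: a minimal form has six parameters (intercept, type, hours, type × hours, human resources, infrastructure). Two rows give rank 2 and residual degrees of freedom 2 − 2 = 0.

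**2. Patient as the unit (280 rows).** A variable constant within each hospital takes two values and is therefore a linear function of the site indicator.

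- If all five covariates are constant within hospital, the rank is 2 of 6: an intercept and one site contrast.
- If one further covariate that varies by patient is added, the rank is 3 of 7. That covariate is estimable.
- If human resources itself varies by patient, the rank is 3 of 6 (intercept, site, human resources).
- Facility type equals site in every case. Hours and type × hours are aliased with site if hours are one value per hospital. If hours varied within a hospital, the product could be estimated, but it would show moderation by hospital, not by sector.

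**3. Error rate if a patient-level test is read as a sector effect.** Take total variance 1, m = 140 per hospital and between-hospital intraclass correlation ρ. The variance of the difference in hospital means is 2[ρ + (1−ρ)/m]. The patient-level test uses 2(1−ρ)/m. The ratio is R = 1 + mρ/(1−ρ), and the real one-sided error is 1 − Φ(1.645/√R).

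| ρ (assumed) | R | 1.645/√R | One-sided error |
|---|---|---|---|
| 0 | 1 | 1.645 | 5% |
| 0.01 | 1 + 1.4/0.99 = 2.41 | 1.06 | 14% |
| 0.05 | 1 + 7/0.95 = 8.37 | 0.57 | 28% |
| 0.10 | 1 + 14/0.90 = 16.56 | 0.40 | 34% |

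The values of ρ are not in the article. One hospital per sector gives no data from which to estimate ρ or to show that it is zero.

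**The case against.** **A regression can be run.** Table 1 schedules CMR team time and cost analysis at admission, every third day and at discharge, so cost inputs are recorded along each stay. This stands. A reader might infer that the regression cannot be fitted at all; that is true only with the facility as the unit. With patient rows a reduced model has ample residual degrees of freedom, and patient-varying inputs may be estimable. Likewise, rank 2 of 6 and a never-estimable interaction hold only if the covariates concerned are constant within a hospital, which the article does not say.

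**More facilities may be meant.** The cost paragraph's unspecified facilities, and its plan to tabulate facility type by frequency, could point to costing beyond the two hospitals. This is weak evidence, since none is named, but it makes the article inconsistent on the point. The remedy must leave room for that reading.

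**The error rates are conditional.** This also stands. They rest on assumed intraclass correlations and matter only if a hospital difference is generalised to sectors. As a test of these two hospitals' mean costs, the patient-level comparison is not inflated by this mechanism.

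**It is peripheral.** The primary end point is facilitators and barriers. The cost end point is the cost of implementation, which needs neither the sector test nor the regression, and the regression is introduced as exploratory. This limits the severity.

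**The analysis plan will settle it.** This does not stand. The article itself fixes the test, the regression and the interaction, and no later detail creates replication from two sites.

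**Conclusion.** The point holds in limited form. On the two-hospital design that the article describes, a public/private effect and the effect of any variable constant within a hospital are aliased with site and have no replication. At facility level the planned inference does not exist (0 degrees of freedom; smallest one-sided P 0.50). At patient level it describes a difference between two hospitals. Read as a sector effect, a nominal 5% one-sided test would err about 14% to 34% of the time for assumed intraclass correlations of 0.01 to 0.10.

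Two assumptions carry this: no further facility is costed, and the two hospitals are in different sectors. If both are in the same sector, there is no comparison to make.

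A reader might go further and infer that the cost end point itself is compromised. The documents do not support that: describing the cost of CMR at each hospital remains valid. The matter is therefore a should-fix on a secondary end point and touches neither the efficacy analysis nor the primary end point.

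**What to change.** In the cost paragraph, remove the public-versus-private test, the facility-level predictors and the facility type by operational hours interaction. Report CMR cost for each hospital with a confidence interval that reflects patient-level variation within that hospital. If a contrast is wanted, give the difference with its interval and label it as a difference between these two hospitals, with no sector or facility-predictor claim. Covariates that vary by patient may stay in an exploratory patient-level model that includes site.

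If further facilities are to be costed, reconcile the cost paragraph with Study Settings, Study Participants and Sample Size Estimation and Analysis by stating their number, their sector and the unit of analysis.

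The first route changes wording only and needs no new data. What is given up is a sector comparison that two sites cannot support.

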### Study Variables and Tools

The study variables, namely, patient demographics (name, age, contact information) and medical history, including current and past medical conditions, allergies, and adverse drug reactions, will be collected with the help of a predesigned case record form that includes tools such as the MAI tool, the STOPP/START tool, and the AT-HARM10 tool, which will be used for data analysis. The economic evaluation will be conducted from a health system perspective. Detailed information will be collected on the facility characteristics, human resources, infrastructure, equipment, and operational costs, allowing for an extensive evaluation of the economic impact of the CMR process from a health system perspective. The collected information in the case record forms will also be entered electronically into the Research Electronic Data Capture (REDCap) software (Vanderbilt), improving the data quality and enabling central access to data (since this is a multicentric study).

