### Data Management and Statistical Analyses

#### Quantitative Component

The investigators will ensure the completeness, accuracy, and timeliness of data collection. The study sites will enter data in the REDCap software, and case record forms will be scanned in REDCap. The data will be checked for a normal distribution (Kolmogorov-Smirnov test). Student paired 1-sided *t* test will be used to analyze the differences between MAI scores at admission and discharge to determine the effectiveness of CMR, and the chi-square test or Fisher exact test will be used to assess the differences in the frequency distribution. All analyses will be conducted via the SPSS software (version 22.0 for Windows 11; Microsoft), Microsoft Excel 2019, and STATA (version 12; StataCorp LP).

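### A normality check decides whether the public-private cost comparison tests mean cost or rank order, although the economic evaluation needs mean cost

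*Protocol article*

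**What the plan says.** The cost analysis is the last paragraph of Data Management and Statistical Analyses; it stands under the Qualitative Component subheading. It states the comparison as follows: "Comparative analyses will assess cost differences between public and private sector facilities". The test is to be an independent-sample, 1-sided t test "for normally distributed data or Mann-Whitney *U* tests for nonnormally distributed data". P values below .05 count as significant.

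The cost paragraph does not name the check that triggers the switch. The Quantitative Component paragraph just before it does name one: "The data will be checked for a normal distribution (Kolmogorov-Smirnov test").

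The same cost paragraph summarises continuous cost variables by "measures of central tendency (mean, median) and dispersion (SD, IQR") and explores predictors of cost by "multivariable linear regression with total CMR costs as the dependent variable". Study Variables and Tools adds: "The economic evaluation will be conducted from a health system perspective". The Results section lists cost-effectiveness calculations among the work to be completed.

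The article does not say whether a cost difference means a difference in means, in medians or in rank order. It also does not give the unit of the comparison (facility, patient, review or cost item).

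**The concern.** The two branches do not test the same thing. A t test asks whether mean costs differ. Mann-Whitney asks whether the two distributions are identical, and it gains power when a random cost from one group tends to exceed a random cost from the other. The two questions agree if the groups differ only by a shift. They separate when the groups differ in spread or shape.

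For a health system the quantity that matters is the arithmetic mean, because mean cost times the number of patients gives the budget. The linear regression on total cost targets the mean, and a cost-effectiveness calculation uses it. A rank-test P value cannot support a statement about which sector costs more in that sense. Cost data are often right-skewed, so the rank branch could well be the one used.

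A sector with many cheap reviews and a few very costly ones could thus be reported as cheaper at the same mean cost. The reverse can also happen: a real difference in mean cost can go undetected.

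**Working it through.** **Inputs from the article.** Two sites with 140 participants each (Sample Size Estimation and Analysis); the two tests and the .05 threshold (cost paragraph); the Kolmogorov-Smirnov check (Quantitative Component). The article gives no cost figure or cost distribution, so there is no stated cost result to reproduce first.

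**Assumptions.** Costs are lognormal in both groups with the same mean, 1000, and log-SDs s1 and s2. Tests are two-sided at 5%. Group sizes are 140 (if patients at the two hospitals are the units) and 10 and 30 (if the units are fewer).

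**Step 1: what Mann-Whitney responds to.** With equal means the log-means are log(1000) − s²/2, so the medians are 1000·exp(−s²/2), and

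P(A>B) = Φ[ (s2² − s1²)/2 ÷ √(s1² + s2²) ].

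For s1 = 0.5 and s2 = 1.0 this is Φ(0.375/1.118) = Φ(0.335) = 0.631. The medians are 882 and 607, while both means are 1000.

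**Step 2: approximate rejection rate at 140 per group.** Under the null, the standard error of the estimate of P(A>B) is √[(2n+1)/(12n²)] = √(281/235200) = 0.0346. The normal approximation to the two-sided rejection rate is then:

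- 0.5 vs 0.6: P(A>B) = Φ(0.055/0.781) = 0.528; 0.028/0.0346 = 0.81; rejection about 13%.
- 0.5 vs 0.7: Φ(0.12/0.860) = 0.555; 1.60; about 36%.
- 0.5 vs 0.8: Φ(0.195/0.943) = 0.582; 2.37; about 66%.
- 0.5 vs 1.0: 0.631; 3.80; about 97%.

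**Step 3: simulation** (3000 data sets per row, equal true means, two-sided 5%).

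| n per group | log-SDs | Mann-Whitney rejects | Welch t rejects |
|---|---|---|---|
| 140 | 0.5 vs 0.5 | 5.0% | 4.9% |
| 140 | 0.5 vs 0.7 | 36.5% | 5.7% |
| 140 | 0.5 vs 0.8 | 65.4% | 5.9% |
| 140 | 0.5 vs 1.0 | 96.0% | 6.1% |
| 30 | 0.5 vs 0.7 | 11.6% | 5.7% |
| 30 | 0.5 vs 1.0 | 42.6% | 7.8% |
| 10 | 0.5 vs 0.7 | 5.5% | 4.5% |
| 10 | 0.5 vs 0.8 | 9.1% | 6.6% |
| 10 | 0.5 vs 1.0 | 15.2% | 9.3% |

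Repeat runs at 140 per group gave 36%, 67% and 97% for the three unequal pairs. A further run gave 13% for 0.5 vs 0.6, in line with Step 2. Across runs at 140 per group, two-sided Welch rejected in 4-7%.

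**Step 4: the reverse error.** With equal medians and log-SDs of 0.5 and 1.0, the means are exp(0.125) = 1.13 and exp(0.5) = 1.65. At 140 per group Mann-Whitney rejects in 6.7% and Welch in 86.9%.

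**Step 5: would the rank branch be reached?** At 140 per group, a Kolmogorov-Smirnov check flagged the more skewed group as non-normal in 97-100% of data sets for log-SD pairs 0.5 vs 0.7 to 1.0.

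**The case against.** The strongest reply is that the simulated comparison is not the one stated. The cost paragraph speaks of facilities, with salaries and utility costs as its examples; it mentions no per-patient comparison. There are two sites, so a facility-level contrast has at most one unit per sector, neither test can be run, and the choice between them does not matter. This stands as a limit. Table 1 does schedule CMR team time and cost analysis at admission, every third day and discharge, so a patient- or activity-level comparison is a fair reading. It is still an inference, as is equating sector with hospital, since the article labels neither hospital public or private.

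Second, the effect depends on sample size and on the gap in spread. At 10 per group, or with a small gap such as 0.5 vs 0.6, it is modest. That also stands.

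Third, no estimand is named. When medians are 882 and 607 typical costs do differ, and Mann-Whitney is correctly rejecting its own null. This is true of the test, but it does not help a budget statement, and the perspective and regression in the article point to the mean.

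Fourth, means, SDs and a mean-based regression are already planned, so a reader would not see a rank P value alone. This lowers the stakes, but the stated test would still not match those summaries.

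A reader might also take the Mann-Whitney test to be one-sided, which would give larger rejection rates in the affected direction. The text attaches one-sidedness only to the t test and is silent for Mann-Whitney, so only two-sided rates are used here.

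**Conclusion.** The point holds as a minor one. The article fixes a rule under which the observed distribution decides whether the sector comparison addresses mean cost or rank order, and only the first fits its economic purpose. The consequence is conditional: it needs patient- or activity-level costs, skewness, and a difference in spread between sectors. Under the assumed lognormal costs with equal means, Mann-Whitney's two-sided rejection rate ranges from about 6% (10 per group, 0.5 vs 0.7) to about 97% (140 per group, 0.5 vs 1.0), and stays at about 5% when spreads are equal.

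A reader might infer that the plan will report a false cost difference between the two hospitals, or that the cost results as a whole are unsound. The documents do not support either reading. They give no cost distribution and do not state the unit. The cost end point is the cost of implementing CMR, which this test does not touch. The public-private contrast is neither an objective nor an end point, and it affects neither the sample size nor the primary end point.

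**What to change.** In the cost paragraph, name the between-sector difference in arithmetic mean CMR cost as the target and state the unit to which it applies. Report each sector's mean and the difference with a 95% interval (Welch, or a bootstrap over the units) whatever the normality check shows. Keep medians and IQRs as description, with Mann-Whitney at most supportive.

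The change takes a sentence or two of wording and a few lines of Stata code, and no new data. The downside is that intervals will be wider when costs are very skewed, which reflects real uncertainty about mean cost. With very few units Welch is itself imperfect (9.3% at 10 per group for 0.5 vs 1.0), so an interval from such numbers should be read with caution.

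### With only two hospitals, the planned public-private cost tests, facility-level cost regression and facility interactions cannot separate sector or facility effects from one hospital differing from the other

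*Protocol article*

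**What the plan says.** Three places fix the number of facilities. Study Settings states: "The study will be conducted at the Pondicherry Institute of Medical Sciences and Jawaharlal Institute of Postgraduate Medical Education and Research". Two further bodies are named there, as collaborators only. Sample Size Estimation and Analysis says "Given that this study will be conducted at 2 different sites" and then "140 participants will be recruited from each site". Study Participants also speaks of two sites.

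The cost paragraph that closes Data Management and Statistical Analyses (printed under Qualitative Component) commits to three inferential analyses:

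- A sector comparison: "Comparative analyses will assess cost differences between public and private sector facilities by using independent-sample 1-sided" *t* tests, or Mann-Whitney *U* tests if the data are not normal.
- A model for what drives cost differences between facilities: "multivariable linear regression with total CMR costs as the dependent variable and facility characteristics, human resources, and infrastructure costs as the independent variables".
- Moderation: "Interaction terms such as facility type and operational hours will be included to investigate the moderating effects".

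Results are to be called significant below .05. The same paragraph says "Data collected from various facilities will be cleaned and entered into a predesigned database", but neither it nor any other section gives a number of facilities or names one beyond the two hospitals. The unit of analysis for cost is not defined. Table 1 schedules CMR team time and cost analysis at admission, every third day and at discharge, so some cost inputs may vary by patient. Phase 5 and Study Variables and Tools describe facility characteristics, infrastructure, equipment and operational costs, which are collected about the facility.

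**The concern.** Sector, operating hours and similar characteristics belong to the hospital, not to the patient. With two hospitals each takes at most two values, and those values change together. Estimating a sector effect, a set of facility predictors and a moderating effect needs several facilities per sector. The plan has at most one.

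The cost of implementation is a stated secondary objective, the first listed secondary end point and the subject of a whole phase. The Discussion says the economic data will be directly relevant to policy makers and administrators. A reported public-private difference, cost predictor or moderator would reach that audience as a statement about sectors and facility types, when the data can show only that one hospital's costs differed from the other's.

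**Working it through.** **Inputs.** Facilities: 2 (Study Settings; Sample Size Estimation and Analysis). Patients: 140 per site, 2 × 140 = 280 (same section). Threshold: P<.05 (cost paragraph). The plan gives no sample size or precision for the cost models, so there is no figure of its own to reproduce on this point. The 280 was derived for CMR efficacy.

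**Facility as the unit.**

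- Two-group *t* test: residual df = 1 + 1 − 2 = 0. There is no within-sector variance, so no test exists.
- Exact Mann-Whitney, 1 versus 1: there are two equally likely orderings, so the smallest one-sided P = 1/2 = 0.50. P<.05 is impossible.
- A minimal form of the regression has 6 columns: intercept, facility type, operational hours, human resources, infrastructure cost, type × hours. Two rows give rank 2. The model cannot be fitted.

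**Patient as the unit.** The two-group test now has 280 − 2 = 278 df and can be computed. The rank of the 6-column design depends on which inputs vary within a hospital:

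| Inputs varying by patient | Rank (of 6) | Coefficients individually identifiable |
|---|---|---|
| None | 2 | 0 |
| Human resources | 3 | 1 (human resources) |
| Human resources and infrastructure | 4 | 2 (both inputs) |

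In every row, facility type, hours and type × hours lie in the space spanned by the intercept and one site indicator. Coding type as 0/1, type × hours equals type multiplied by the second hospital's hours, which is the site indicator rescaled. One site contrast is estimable. A separate sector effect, an hours effect and their interaction are not.

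**False precision if patients stand in for sectors.** Suppose sector has no true effect and hospitals differ with site-level ICC ρ. The true variance of the difference in means is 2σ²[ρ + (1−ρ)/140]. The *t* test assumes 2σ²(1−ρ)/140. The ratio is R = 1 + 140ρ/(1−ρ), and a nominal 5% one-sided test rejects with probability 1 − Φ(1.645/√R) (normal approximation). The documents give no ICC, so ρ is an assumption shown over a range:

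| ρ (assumed) | R | 1.645/√R | Rejection rate |
|---|---|---|---|
| 0.01 | 2.41 | 1.059 | 14% |
| 0.05 | 8.37 | 0.569 | 28% |
| 0.10 | 16.56 | 0.404 | 34% |

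**Circularity.** Phase 5 counts human resources and infrastructure, with equipment and operational costs, among the costs of CMR. Where the first two enter the regression as costs, part of the outcome is being regressed on itself.

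**The case against.** The strongest reply is that the unit of analysis is left open and Table 1 lets costs vary by patient. On that reading the two-group test runs with 278 df, and coefficients for patient-varying inputs can be estimated. This stands. A reader might infer that none of the planned models can be estimated at all, and the document does not support that. It is true with the facility as unit, and true of the facility-level terms at either level, but not of every patient-level coefficient.

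Two further inferences are tempting and also go too far.

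- Rank 2 at patient level is not a fixed property of the plan. It assumes human-resource and infrastructure inputs are constant within each hospital. Nor does rank 2 of 6 mean that four coefficients are lost and two kept: none of the six is then individually identifiable.
- The regression is not shown to be an accounting identity with R² near 1. Human resources may mean staffing rather than cost, and equipment, operational, indirect and opportunity costs are counted too. If both inputs are constant within site, patient-level R² is only the between-site share, d²/(d² + 4) for a site difference of d SD. That is 0.25/4.25 = 0.06 for d = 0.5 and 1/5 = 0.20 for d = 1. Partly circular is what can be said.

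It may also be said that "Data collected from various facilities will be cleaned and entered into a predesigned database" implies more costing sites. Nothing else in the article names or counts any, and if more are meant the paragraph still has to say so. The article does not state which hospital is public and which private, but with two sites there is at most one per sector either way.

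Finally, cost is a secondary end point, the regression is presented as exploratory, descriptive cost summaries are already planned, and the Discussion limits generalizability beyond tertiary care. All of that is fair, and the cost estimates themselves are unaffected. None of it rescues the sector, predictor and moderator inferences.

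**Conclusion.** The analyses are wrong as written, and the protocol specifies them itself, so they are not a detail left to an analysis plan. With two hospitals, the public-private comparison and the facility interactions fail at either unit of analysis. By facility there are 0 residual df and a minimum one-sided P of 0.50. By patient there is one estimable site contrast, which cannot be attributed to sector, hours or their interaction.

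The conclusion rests on the two-site count, which the article gives consistently. The 14% to 34% rejection rates are illustrative, because they depend on assumed ICCs. Circularity applies only so far as the regressors are costs. What remains sound is a description of cost at each hospital, a contrast labelled as a difference between these two hospitals, and estimates for inputs that vary by patient and are not themselves part of the outcome.

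**What to change.** In the cost paragraph:

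1. Delete the public-private hypothesis tests, the regression on facility-level characteristics and the interaction terms.
2. Report CMR costs descriptively by site, using the summaries already planned, and call any contrast a site difference.
3. If predictors are wanted, model a patient-level outcome such as CMR team time (Table 1) on patient-level variables, for example the number of CMR consultations (Process Indicators of Intervention), with site as a fixed effect.
4. If further costing facilities are intended, state their number and sector, and define the unit of analysis.

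This rewords one paragraph. Options 1 to 3 need no new data collection if the chosen patient-level variables are among those already recorded. The price is giving up a public-private claim that the data could not have supported.
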